### Complications, adverse events, additional surgery

The investigators will record all complications and adverse events accurately. These will be grouped in the following categories:

● Infections, grouped as superficial wound infections and deep wound infections

● Post-surgical hematoma

● Increased neurological symptoms

● Venous thrombosis

● Other (serious) adverse events

All adverse events and complications will be monitored and followed up until stable or resolved during the course of the study. Each adverse event will be reported to the operating surgeon and will be associated to the type of cage used to qualify the event to be related. Code breaking will occur by the clinical observer or operating surgeon if the clinical condition of the patient necessitates this*.* Early termination of the study will be decided if necessary.

#### Additional surgery

All additional surgeries during the follow-up period that are related to surgery will be recorded. Any additional spine surgery at the operated level will be considered as a complication and a poor result.

### Withdrawal of participants from the trial

A participant may be withdrawn from the clinical study for the following reasons:

● Patients may choose to withdraw from the study under the terms of the Declaration of Helsinki and their consent documentation without having to give a reason

● Any unanticipated adverse reaction which is, in the opinion of the researcher, related to the treatment and will endanger the well-being of the patient if treatment is continued

● The development of any intercurrent illness(es), infection or condition(s) that might interfere with the clinical investigation

● Non-compliance with the study procedures deemed by the investigator to be sufficient to cause discontinuation

● Any problem deemed by the Investigator to be sufficient to cause discontinuation

All patients discontinued from the investigation due to an unanticipated adverse reaction, directly related to the investigation, will be treated until the reaction resolves. The researcher will clearly document the date and reason(s) for the patient withdrawal. Patients who have withdrawn from the study will not be replaced if they have received investigation treatment. If possible, any procedures or assessments planned for the patient on withdrawal from the investigation should be performed when intention to withdraw the patient is announced. Patients who are withdrawn prior to receiving treatment will be replaced.

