#### Statistical analysis

The primary analysis will be on the change from baseline in RMDQ score. This will be analyzed based on a mixed model for repeated measurements, including baseline RMDQ as covariate and treatment and center as factors. No imputation will be applied for this analysis. The primary comparison will be at 12 months of follow-up.

Sensitivity analyses to assess impact of drop outs will be performed. These will include an analysis based on Last Observation Carried Forward imputation, as well as multiple imputations based on differential patterns of drop out/missing data reasons.

An exploratory analysis of the distribution of the individual improvements in change from baseline in RMDQ score versus the fusion rate (in three categories) within treatment groups will be performed to assess the extent to which both are consistent.

Other continuous outcomes assessed at each visit will be analyzed similarly. Dichotomous outcomes will be compared between treatment groups based on Z-tests for comparing proportions, with results expressed as 95% confidence intervals for the difference in proportions.

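### Implanted patients may be withdrawn from the study for reasons plausibly tied to outcome, with no later RMDQ provided for; if such losses fall more on the silicon nitride arm, the 12-month comparison leans toward non-inferiority

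*Protocol article*

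**What the plan says.** The section *Withdrawal of participants from the trial* opens: "A participant may be withdrawn from the clinical study for the following reasons". The wording is permissive, and what the patient leaves is the study. Besides the patient's own choice, four reasons are listed:

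- a reaction that was not anticipated, that the researcher attributes to the treatment, and that would put the patient at risk were treatment to go on;
- illness or infection, worded as "The development of any intercurrent illness(es), infection or condition(s) that might interfere with the clinical investigation";
- failure to follow the study procedures, where the investigator judges it serious enough;
- a catch-all without a criterion, worded as "Any problem deemed by the Investigator to be sufficient to cause discontinuation".

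The section asks that planned assessments be done when the withdrawal is announced, if possible. It requires the date and reasons to be documented and does not replace patients who have been treated. It says nothing about RMDQ at the visits that remain.

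Under *Surgical management* the treatment is one operation. The section on complications and adverse events lists wound infections as recorded complications and has adverse events followed until stable or resolved.

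Under *Statistical analysis* the primary analysis is a mixed model for repeated measurements of change in RMDQ, compared at 12 months: "No imputation will be applied for this analysis". The sensitivity analyses are "an analysis based on Last Observation Carried Forward imputation" and, in the same sentence, multiple imputation by pattern of drop-out or reason for missing data. Under *Sample size* there are 50 patients per arm and no addition for drop-out.

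**The concern.** Once the cage is in place there is no course of treatment left to stop, so the condition about continuing treatment has little to act on. Withdrawing an operated patient for one of these four reasons removes future questionnaires and nothing else.

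The reasons are not neutral. An infection, a treatment-related reaction or an unspecified problem after spinal fusion plausibly goes with a poor functional result, and two of the four reasons rest on the investigator's discretion. The mixed model uses the visits before withdrawal, but beyond that it assumes that withdrawn patients would have continued like similar patients who stayed. If they do worse than their earlier scores predict, and this happens more in the silicon nitride arm, part of a real deficit disappears from the estimate. In a non-inferiority trial that is the anti-conservative direction.

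Such a difference between arms is possible: the complications section has each adverse event associated with the type of cage when its relatedness is judged, and relatedness is one of the withdrawal criteria. Lost scores also cost power, for which nothing was set aside.

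**Working it through.** **1. The plan's own figure.** Inputs from *Sample size*: SD 4, margin 2.6, one-sided 2.5%, power 90%, true difference 0.

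n per arm = 2 × (4/2.6)² × (1.960 + 1.282)² = 49.7, so 50. This reproduces; power at 50 per arm is 90.1% by normal approximation and 89.6% by noncentral t.

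Standard error of the difference = 4 × √(2/50) = 0.80.

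**2. Upper bound on the bias.** The documents give no withdrawal rate, so these inputs are assumptions: patients who stay improve by 10 points (the mean improvement cited under *Sample size*), withdrawn patients would have improved by 2, and earlier visits recover nothing.

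Bias toward silicon nitride = (rate in silicon nitride − rate in PEEK) × (10 − 2).

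If the true deficit equals the margin, the chance of declaring non-inferiority is Φ(bias/0.80 − 1.96).

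| Withdrawal, silicon nitride v PEEK | Bias (points) | Share of margin | False non-inferiority |
|---|---|---|---|
| equal | 0 | 0% | Φ(−1.96) = 2.5% |
| 8% v 4% | 0.04 × 8 = 0.32 | 12% | Φ(−1.56) = 5.9% |
| 10% v 2% | 0.08 × 8 = 0.64 | 25% | Φ(−1.16) = 12.3% |
| 4% v 8% | −0.32 | −12% | Φ(−2.36) = 0.9% |

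The last row shows the reversal when PEEK loses more.

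**3. What the mixed model recovers.** A simulation used assumed mean improvements of 6, 8 and 10 points at 3, 6 and 12 months, with withdrawn patients 5, 7 or 10 points worse at 12 months and no other cage effect. The mixed model was approximated by sequential regression under monotone drop-out. Differences are silicon nitride minus PEEK; positive means silicon nitride is worse.

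| Withdrawal | True difference | Mixed model | LOCF |
|---|---|---|---|
| 10% v 10% | about 0 | about 0 | about 0 |
| 15% v 5% | 0.5 to 1.0 | 0 to 0.8 | 0.2 to 1.4 |
| 20% v 5% | 0.75 to 1.5 | 0 to 1.2 | 0.3 to 2.1 |

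At 15% v 5% the mixed model hides about 0.1 to 1.0 point. It hides least when the poor course already shows before withdrawal and most when it does not. A bias of 0.5 or 1.0 point would raise false non-inferiority to about 9% or 22–24% (45 to 50 patients per arm).

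**4. LOCF.** At 15% v 5%, with patients 5 points worse at 12 months, LOCF overstated the deficit when they left before the 3-month visit (1.01 against a true 0.52). It understated the deficit when they left before the 12-month visit with no earlier sign of trouble (0.21 against 0.50).

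**5. Power.** Loss of 10% lowers power to 86% (t-test) or 89% (baseline-adjusted, correlation 0.3). Loss of 20% lowers it to 82% or 85%.

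**The case against.** Several stronger readings are tempting, and the documents do not support them.

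- *Every patient with an infection or complication is taken out.* The rule is permissive and covers only conditions that might interfere with the investigation and reactions that are unanticipated, related and endangering. Wound infections are otherwise recorded and followed. This stands.
- *The analysis necessarily favours non-inferiority.* It does so only if poor-outcome withdrawals are more frequent or worse in the silicon nitride arm. The article's own rationale expects fewer complications with silicon nitride, which would point the other way, and lost data lower power, which works against showing non-inferiority. This stands too: the direction is a risk and cannot be known in advance.
- *No imputation means complete cases only.* It does not. Visits at 3 and 6 months still contribute, so 0.32 and 0.64 points are upper bounds.
- *LOCF favours non-inferiority.* It can err in either direction, as step 4 shows.
- *LOCF is the only check.* Multiple imputation by pattern or reason is planned, and the documented reasons for withdrawal feed it. Its details may sit in an analysis plan that is not shown, so their absence is no fault. It cannot fully repair the loss, however: if collection stops at withdrawal, no later RMDQ from patients withdrawn for that reason exists to inform the imputation, and the result rests on assumption.

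Finally, the article is condensed, and the full protocol may provide for questionnaires after withdrawal. If so, the main change is already in place. But the article states a rule of withdrawal from the study with one assessment at exit, and on that text the point holds.

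**Conclusion.** The point holds as a conditional risk created by a stated rule. Implanted patients can leave follow-up for reasons plausibly related to outcome, some of them discretionary, and nothing in the article keeps their 12-month RMDQ. The primary model is then valid only under missing at random.

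Under the assumptions in step 2 the bias is at most 0.32 points at 8% v 4% and 0.64 points at 10% v 2%, with false non-inferiority up to about 5.9% and 12.3% against 2.5%. It is about zero with balanced withdrawal and reverses if PEEK loses more. All rates are assumed, because the documents give none.

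The trial is not shown to be biased. The change is nevertheless worth making, because it is cheap, protects power in a trial without a drop-out allowance, and secures data that cannot be recovered later. The choice of LOCF is secondary.

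**What to change.** **Main change.** For implanted patients, limit withdrawal from follow-up to withdrawn consent. For the other listed reasons, record the event and its date, keep collecting RMDQ and the secondary questionnaires at every remaining scheduled visit up to 24 months, and analyse the data in the allocated arm. This concerns data collection only and leaves clinical care as it is.

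**Secondary change.** LOCF does not test missing at random. Let the multiple imputation already planned include a delta-adjusted analysis: make missing 12-month scores in the silicon nitride arm worse in steps, from 0 to at least 2.6 points, and report the step at which non-inferiority is lost.

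**Cost.** A short amendment of the withdrawal section, one further specified sensitivity analysis, slightly more follow-up work, and possibly somewhat noisier scores from patients who would otherwise have left.

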### Randomization

Patients who meet the inclusion and exclusion criteria, and have given informed consent are allocated the next available investigational number (Patient ID number) and will be randomly allocated to one of two groups (treatment A or treatment B) by use of a centralized 24-hour computerized randomization system that allows internet randomization (Sealed Envelope Ltd. London). After completing follow-up at 2 years post-surgery both patient and researcher will be informed which cage was used.

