### Outcome measurements

Several validated questionnaires described below will be used for outcome assessments. During intake, a basic physical exam with neurological examination (muscle strength, reflexes) and additional assessments as required per normal practice will be performed to ensure that the patient can undergo surgery safely. During follow-up visits at 3, 6, 12 and 24 months the neurological examination will be repeated. See Table 2 for the patient follow-up chart.

**Table 2 T2:** Follow-up chart

	**Intake**	**Admission**	**3 months**	**6 months**	**12 months**	**24 months**
Visit	1	2	3	4	5	6
Demography	X					
Study information + informed consent	X					
Randomization	X					
Surgery		X				
Operative data		X				
Neurological examination	X		X	X	X	X
Questionairres:	X		X	X	X	X
- Roland Morris disability questionairre						
- SF-36						
- VAS back						
- VAS leg						
- Working status						
Likert scale		X	X	X	X	X
X-rays	X	X	X	X	X	X
CT					X	
MRI	X					
Complications		X	X	X	X	X

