### Data management

All data recorded during intake, hospitalization and follow-up visits will be de-identified. Participants will be identified by a unique investigational number (Patient ID number) allocated during intake. Primary and secondary outcome variables, information gathered during intake and hospitalization and all complications, additional surgery, adverse events and withdrawals will be entered by the researcher into an electronic data capture system (Acumen Healthcare Solutions, LLC, Plymouth, Minnesota, USA). The source documents will be stored in the hospital where the patient underwent the surgical procedure and shall be retained for a period of minimal 5 years after the study completion or longer if deemed necessary.

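### Patients are randomized at intake but replaced if withdrawn before surgery, so allocated patients can leave the comparison; arm-related bias is possible but not shown

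*Protocol article*

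**What the plan says.** Three parts of the protocol article fix the time of allocation. The Randomization section states that "Patients who meet the inclusion and exclusion criteria, and have given informed consent are allocated the next available investigational number (Patient ID number)" and are randomly allocated to treatment A or B, through a "centralized 24-hour computerized randomization system that allows internet randomization". Data management says that each participant has a "unique investigational number (Patient ID number) allocated during intake". In Table 2 (Outcome measurements) the row "Randomization" is marked under Intake, visit 1, while Surgery is marked under Admission, visit 2.

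The section on withdrawal of participants then gives two rules. For operated patients: "Patients who have withdrawn from the study will not be replaced if they have received investigation treatment". For the others: "Patients who are withdrawn prior to receiving treatment will be replaced". The grounds for withdrawal are not limited to the time after surgery. They include intercurrent illness and, as a catch-all, "Any problem deemed by the Investigator to be sufficient to cause discontinuation".

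Under Sample size, 100 patients in total are to be randomized, 50 per arm, with no allowance for drop-out. The opening of Methods/Design describes patients and clinical observers as blind during follow-up.

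**The concern.** A replacement rule does no harm when it applies before allocation, because it then only refills the screening pool. Here it applies after allocation. A patient who leaves between intake and admission already belongs to an arm, and the rule treats that place as one to be refilled by someone else. The 50 per arm then tend to become 50 operated patients per arm, which is not the set that randomization made comparable.

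What is at stake depends on whether departures in this interval can be related to the arm. The article does not describe concealment between intake and surgery, and one ground for withdrawal is open-ended. If departures did depend on the arm and on prognosis, the treatment difference would be shifted. In a non-inferiority trial, a shift in favour of the new cage raises the chance of a false claim.

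There is also a plain inconsistency: with replacement, the number randomized exceeds the stated 100.

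**Working it through.** **Step 1: timing.** Randomization is at visit 1 (Table 2, and the patient number given at intake). Surgery is at visit 2. The replacement rule covers everyone withdrawn before treatment, so it covers patients who have already been allocated.

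**Step 2: number randomized.** If w patients are replaced, at least 100 + w are randomized. To end with 100 operated patients when a share d is lost before surgery, 100/(1 − d) must be randomized. The article gives no d. For assumed values of 2%, 5%, 10% and 15%, the result rounded up is 103, 106, 112 and 118.

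**Step 3: the plan's own figure.** Inputs from Sample size: SD 4, margin 2.6, one-sided 2.5%, 90% power, and a true difference of 0 (implied).
- n per arm = 2 × 4² × (1.96 + 1.28)² / 2.6² ≈ 49.7, so 50.
- SE = 4 × √(2/50) = 0.80.
- Power = Φ(2.6/0.80 − 1.96) = Φ(1.29) = 90.1%. The noncentral t gives 89.6%.

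The stated sample size reproduces. The point does not rest on an error there.

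**Step 4: possible shift.** Suppose a share f of one arm only is exchanged for patients whose expected improvement is D points greater. The arm mean moves by f × D. If this favours silicon nitride, the one-sided error at the margin is Φ(f × D/0.80 − 1.96). Both f and D are assumptions; the article gives neither.

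| f (one arm) | D (points) | Shift (points) | One-sided error |
|---|---|---|---|
| none, or same loss and same D in both arms | – | 0 | 2.5% |
| 2% | 4 | 0.08 | 3.1% |
| 5% | 4 | 0.20 | 4.4% |
| 10% | 2 | 0.20 | 4.4% |
| 10% | 3 | 0.30 | 5.6% |
| 10% | 4 | 0.40 | 7.2% |

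For the 10%, 3-point case: 0.10 × 3 = 0.30; 0.30/0.80 = 0.375; Φ(0.375 − 1.96) = Φ(−1.585) ≈ 5.6%. The shift is 0.30/2.6 = 12% of the margin.

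If the same shift goes against silicon nitride, the error at the margin falls to Φ(−0.375 − 1.96) ≈ 1.0%. Power at a true difference of 0 falls to Φ((2.6 − 0.30)/0.80 − 1.96) = Φ(0.915) ≈ 82%.

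**Step 5: cost of not replacing.** With 100 randomized and 5 per arm giving no outcome, 45 per arm remain. Power by t-test (noncentral t) is 86.2%. With the article's example correlation of 0.3 between baseline and endpoint, the SD becomes 4 × √(1 − 0.3²) = 3.82 and power is 89.2%.

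**The case against.** The strongest reply is that the text does not establish any route from the rule to bias.

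- A reader might infer that the surgeon knows the cage before the operation and can withdraw unsuitable patients. The article does not say so. The surgeon must know the cage when inserting it, but the time at which the allocation is revealed is not given. Allocation is coded A or B, and the researcher, who sees patients at intake and documents withdrawals, learns the cage only after two years. This stands: arm-related withdrawal is a possibility left open and is not described. It does not close the gap, because blinding is stated only for follow-up and the investigator who may withdraw a patient is not identified as blind.
- A reader might infer that a replacement takes over the withdrawn patient's arm and so upsets the balance. Nothing says this. Under the Randomization section a new patient receives the next number and a fresh random allocation. Any bias would come from who leaves, not from adding patients.
- A reader might infer that replaced patients are certainly excluded from analysis and that no analysis could help. The article says only that they are replaced, and an analysis set may be defined in a document not shown. Baseline scores are taken at intake, the date and reason of withdrawal are recorded, assessments at withdrawal are done where possible, and multiple imputation by missing-data reason is planned as a sensitivity analysis. This stands, with a limit: the article does not say that the imputation covers patients withdrawn before surgery. Without follow-up scores, any such analysis rests on assumptions, and the primary model, which uses no imputation, gains nothing from these patients.
- The 5.6% is one unfavourable case built on assumed inputs. This also stands, which is why the table includes zero and the reverse direction is shown.

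**Conclusion.** The point holds as an avoidable exposure in a rule that the protocol states. It does not show that the comparison is biased. Allocation precedes surgery by a visit, pre-operative withdrawals are replaced on grounds that include discretion, and the number randomized would then exceed 100. That much is certain from the text.

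The size is not known. It is zero if losses are unrelated to arm. Under the assumption of a 10% exchange in one arm and a 3-point difference in prognosis, it is 0.30 points: about 5.6% one-sided error instead of 2.5% if the shift favours silicon nitride, or about 82% power instead of 90% if it goes the other way. Smaller assumed exchanges have smaller effects (3.1% at 2% and 4 points). The change is worth making because it is inexpensive and removes the question.

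**What to change.** Preferred: move randomization in Table 2, and in the Randomization and Data management sections, from intake to as close to surgery as practicable, for example the day of surgery. The 24-hour internet system already named can serve this. The patient number can still be given at intake if it is separated from the allocation. Patients who withdraw earlier are then not yet randomized and can be replaced freely, and the total of 100 randomized stands. Cost: a protocol amendment, and both cage types available for each operation. No extra patients are needed.

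If randomization stays at intake:
- delete the replacement rule for randomized patients;
- conceal the allocation until surgery, and say so;
- follow everyone randomized and analyse them in the allocated arm;
- report pre-operative withdrawals and their reasons by arm.

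Cost: a small loss of power, to about 86% by t-test or 89% with a baseline correlation of 0.3 if 5 per arm are lost. Alternatively, allow for early loss in advance by planning to randomize more, for example 106 for an assumed 5%.

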### Data management

All data recorded during intake, hospitalization and follow-up visits will be de-identified. Participants will be identified by a unique investigational number (Patient ID number) allocated during intake. Primary and secondary outcome variables, information gathered during intake and hospitalization and all complications, additional surgery, adverse events and withdrawals will be entered by the researcher into an electronic data capture system (Acumen Healthcare Solutions, LLC, Plymouth, Minnesota, USA). The source documents will be stored in the hospital where the patient underwent the surgical procedure and shall be retained for a period of minimal 5 years after the study completion or longer if deemed necessary.

